### 11.3 Planned Analyses

All statistical analyses will be carried out by the study team experienced in the conduct of cluster-randomized trials.

#### 11.3.1 Datasets to be Analyzed, Analysis Populations

The analyses of primary and secondary outcomes will follow the intention-to-treat principle. Per-protocol analyses will be performed within the scope of sensitivity analyses. In the intervention group we will carry out exploratory analyses to identify factors related to drug deprescription.

#### 11.3.2 Primary Analysis

Descriptive statistical methods will be used to describe the study population, including dropouts and losses to follow up. Baseline characteristics of the intervention and control groups will be calculated with corresponding 95% confidence intervals where applicable.

The primary outcome will be compared between groups using Kaplan-Meier and log rank tests. To compare factors which may affect readmission, Cox regression (proportional hazards model) will be used considering hospital clinics/units as clusters. The multivariable model will include patient characteristics as factors as well as all covariates used for balanced allocation of clusters to the study arms, and subgroup analyses may be carried out for such factors or covariates.

For secondary outcomes, parametric ( $t$ -test) or non-parametric tests ( $\chi^2$ - and Wilcoxon test) will be used where appropriate.

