| Number of Participants with Rationale: | 
Based on published readmission rates, an exponential survival curve has been modeled. We defined a delay in time to readmission of 25% as relevant. This translates into a difference in medians of 23 days (from 93 to 116 days) and corresponds to a hazard ratio of 0.80 between intervention and control group participants. We assumed a two-sided alpha of 0.05, a power of 80%, an intraclass correlation coefficient (ICC) of 0.02, an overall censoring probability of 40%, and a cluster size of 50 patients per senior HP. Thus, 21 senior HPs and 1’050 patients per arm are needed, i.e. 42 senior HPs and 2’100 patients in total.
 
An interim analysis with 50% of the full sample size is planned in case of poor recruitment success.
                                                                                                                                            |
| Study Duration:                        | Patients will be recruited during 4 months or until the designated number of patients per cluster is reached, and follow up will last for 6 months for each patient.                                                                                                                                                                                                                                                                                                                                                                                                                                                                                                                                                                                                                                                                                                                                           |

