| Statistical Considerations: | 
Pilot test: Mixed methods approach to achieve quantitative (e.g. ratings on a 5-point Likert scale) as well as qualitative (e.g. awareness, perception) results.
 
RCT: Intent-to-treat (ITT) approach. Descriptive statistics to describe the study population. Baseline characteristics will be compared between control and intervention group using t-test, Mann-Whitney U test, <math>\chi^2</math>-test or Fisher's test, according to the type of data. The primary outcomes will be compared using Kaplan-Meier and log rank tests. To assess factors which may affect readmission, Cox regression will be used considering senior HPs as clusters. Determinants associated with a change of the medication will be investigated by exploratory, multivariate regression analysis. For secondary outcomes, parametric (t-tests) or non-parametric tests (<math>\chi^2</math>- and U tests) will be used where appropriate.
                                                                                                                                                                                                                                                                                                            |

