### **6.3.1 Randomization**

Randomization will take place on the level of the participating senior HPs (= clusters) whereby senior HPs working in the same clinic/ward/hospital unit will be jointly allocated to the same study arm. Intern physicians will be assigned deterministically to their senior HPs' study arms. The consecutive inclusion of eligible patients by their HPs will not involve further randomization either as any included patient will be allocated to the trial arm (intervention or control group) of her/his recruiting physician.

Randomization on the cluster level to equally sized treatment arms will be performed using a software random number generator by a member of staff not involved in planning of the study nor the recruitment of participants. Greatest possible balance between the study arms, in terms of the covariates listed in section 5.2, will be achieved through a customized minimization procedure described in more detail in section 7.3.

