### 11.2 Determination of Sample Size

We modeled hospital readmission time by fitting an exponential survival curve on published readmission rates (48, 46) and internal data from the University Hospital Zurich. Extending readmission time by 25% was considered a relevant effect of the intervention. In the fitted model, this translates into an increase of the median readmission time by 23.2 days (from 92.7 days to 116.8 days) and corresponds to a hazard ratio of 0.80 between intervention and control group participants. This is equivalent to a decrease of 18.2% in readmission rates after 30 days (from 20.1% to 16.4%).

Based on this hazard ratio and assuming a two-sided  $\alpha = 5\%$ , a power of  $1 - \beta = 80\%$ , an intraclass correlation coefficient (ICC) of 0.02 as in (18), 40% overall censoring probability and equally sized clusters of 50 patients, we calculated a sample size of 21 clusters and 1'050 individuals per trial arm. Thus, 42 senior HPs and 2'100 patients in total will need to be included in order to observe a relevant effect of the study intervention with sufficient power.

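### The primary between-arm test is named as a log-rank test with no adjustment for clustering; under the plan's own ICC its two-sided error rate would be about 16 to 20%, not 5%

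*Protocol*

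**What the plan says.** Section 11.3.2 of the protocol states: "The primary outcome will be compared between groups using Kaplan-Meier and log rank tests". The synopsis, under statistical considerations, agrees: "The primary outcomes will be compared using Kaplan-Meier and log rank tests". No clustered, stratified or permutation form of the test is named in either place or elsewhere in the protocol.

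Clustering appears in three other places:

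- **Randomisation (6.3.1).** The unit is the senior physician, but "senior HPs working in the same clinic/ward/hospital unit will be jointly allocated to the same study arm".
- **Sample size (11.2).** The calculation assumes an ICC of 0.02, equal clusters of 50, 40% censoring and a hazard ratio of 0.80, at two-sided 5% and 80% power. It arrives at 21 clusters and 1,050 patients per arm.
- **Cox model (11.3.2).** "To compare factors which may affect readmission, Cox regression (proportional hazards model) will be used considering hospital clinics/units as clusters". The synopsis gives a different cluster unit for what appears to be the same model: "Cox regression will be used considering senior HPs as clusters".

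**The concern.** A standard log-rank test takes its variance from patients treated as independent. Patients of one senior physician, or of one ward, share prescribing habits, discharge routines and case mix, and the sample size calculation itself assumes that their outcomes are correlated. The plan therefore pays for clustering in patient numbers and then names a primary test that takes no account of it.

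The treatment comparison would have too small a variance and too small a p-value. Since spreading the approach if it succeeds is a stated secondary objective (section 4.3), a false positive would have practical consequences.

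The clustered Cox model does not settle the matter. The sentence before it gives the group comparison to the log-rank test, and nothing says which result governs if the two disagree.

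**Working it through.** **Inputs, all from section 11.2:** hazard ratio 0.80, two-sided alpha 0.05, power 80%, ICC 0.02, cluster size 50, 40% censoring, 21 clusters and 1,050 patients per arm. The control median is 92.7 days.

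**1. Reproduce the planned size.**
- Events (Schoenfeld): 4 × (1.960 + 0.842)² / (ln 0.80)² = 631.
- Patients without clustering: 631 / 0.60 = 1,052.
- Design effect: 1 + (50 − 1) × 0.02 = 1.98.
- Patients with clustering: 1,052 × 1.98 ≈ 2,082, or 20.8 clusters per arm, rounded up to 21. Freedman's formula gives 20.99, also 21.

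The stated figure is reproduced, so 1.98 is a design effect consistent with the plan's own numbers.

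**2. Error rate of an unadjusted test.** If the true variance is DE times the assumed one, a nominal 5% test rejects with probability 2 × [1 − Φ(1.96/√DE)].
- DE = 1.98: 1.96/1.407 = 1.393, giving 16.4% two-sided. Half of this, 8.2%, is false benefit, against 2.5% intended.

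**3. Simulation under no effect.** The set-up was 42 clusters of 50, exponential times with median 92.7 days and six months of follow-up.
- Gamma cluster frailty, dropout added to reach about 40% censoring, 8,000 runs: 19.0% and 18.8% at readmission ICCs of about 0.017 and 0.019.
- Log-normal cluster effect with SD 0.20, 10% loss, ICC about 0.022, 2,000 runs: 20.0%, and 5.3% with no cluster effect. This run has fewer censored patients than the plan assumes.
- At 20%, false claims of benefit are about 10%.

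**4. Sensitivity, by the formula in step 2.**

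| Assumption | Design effect | Two-sided error |
|---|---|---|
| ICC 0.01 | 1.49 | 10.8% |
| Only the 30 expected events per cluster count (50 × 0.60) | 1.58 | 11.9% |
| Plan's own inputs | 1.98 | 16.4% |
| ICC 0.03 | 2.47 | 21.2% |

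**5. After correction.** A cluster-robust log-rank test in the 40%-censoring simulation rejected in 5.4 to 5.9% of null trials. For power, 2,100 × 0.60 = 1,260 events, and 1,260 / 1.98 = 636 effective events. The expected z is ½ × √636 × 0.223 = 2.81, so power is Φ(2.81 − 1.96) = 80.4%. With a t critical value on 40 degrees of freedom (2.02 instead of 1.96) it is about 78%.

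**The case against.** **The protocol says only log-rank tests, and an unseen statistical analysis plan may specify a clustered form.** That is possible, which is why the error rate is stated as conditional. But the protocol is not silent: it names a test twice, without adjustment, and a reader who follows it would run the standard version.

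**A clustered Cox model, adjusted for the allocation covariates, already stands under the heading of primary analysis.** This is true, and it makes the remedy easy. It would be wrong to say that no cluster-aware analysis is planned. However, the model's stated purpose is other factors, the treatment arm is not listed among its terms, and its cluster unit differs between the synopsis and section 11.3.2.

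**The ICC is a planning value borrowed from another trial.** This stands. A reader might infer that the trial's false-positive rate simply is 16 to 20%. The documents support only what it would be with an unadjusted test and the plan's own ICC.

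**Balanced allocation (section 7.3) may remove part of the between-cluster variation.** This also stands, and the calculations above do not model it. The protocol gives no explained share. As an assumption, with near-perfect balance and DE = 1 + 0.98 × (1 − R²), a share of 30% gives DE 1.69 and about 13.1%; a share of 50% gives DE 1.49 and 10.8%. Both remain above 5%.

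**Two further stronger readings fail.** One is that an ineffective intervention would be declared effective in 16 to 20% of trials. That range counts rejections in both directions; false benefit is about half of it. The other is that the rate exceeds 25% because wards are shared. Two senior physicians per ward (100 patients) would give DE 2.98 and 25.6% by formula, but the protocol only allows shared wards and does not say how many there are.

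**Conclusion.** The point holds. As written, the primary between-arm test takes no account of the cluster randomisation that the sample size allows for. If the test is run unadjusted and the ICC for readmission is 0.02, the two-sided type I error is about 16% by formula and 19 to 20% by simulation, instead of 5%.

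The size is conditional. It falls to about 11 to 12% with an ICC of 0.01 or an event-based design effect, may fall below 16% through balanced allocation, and rises by an unknown amount if several senior physicians share a jointly allocated ward. Every case worked here gives at least twice the nominal level, so the need for correction does not depend on the exact ICC. The conflicting cluster unit of the Cox model is part of the same defect, because any cluster-valid test must name its cluster.

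**What to change.** In section 11.3.2 and in the synopsis, designate one cluster-valid primary test. Either of these is adequate:

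- the intervention effect (hazard ratio, 95% confidence interval, p-value) from the Cox model already planned, with shared frailty or cluster-robust variance, a correction for the small number of clusters, and the allocation covariates as adjustment; or
- a cluster-adjusted log-rank test.

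Use the same cluster definition in both places, namely the jointly allocated clinic or ward. Keep the Kaplan-Meier curves as description.

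**Cost.** No new data are needed. Under the plan's own assumptions no extra patients are needed either, since power stays near 80% (about 78% with the small-sample critical value in the working). If wards hold several senior physicians there are fewer than 42 independent units and power would be lower, so the number of wards should be recorded before the analysis is finalised. The p-value will usually be larger than that of an unadjusted test. The edit is short but is not purely editorial: section 2.9 lists changes to the form of statistical analysis among those that the ethics committee must authorise.

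### The log-rank test named for the primary comparison makes no allowance for the clustering built into the sample size; at the protocol's planning ICC its type I error is about 16%, not 5%

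*Protocol*

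**What the plan says.** Section 11.3.2 of the Protocol gives the between-arm comparison: "The primary outcome will be compared between groups using Kaplan-Meier and log rank tests". The synopsis, under Statistical Considerations, matches it: "The primary outcomes will be compared using Kaplan-Meier and log rank tests". Neither sentence names a robust variance, a frailty term or any other allowance for clusters.

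Clustering appears in the next sentence of 11.3.2, for a different purpose: "To compare factors which may affect readmission, Cox regression (proportional hazards model) will be used considering hospital clinics/units as clusters". The terms listed for that model are patient characteristics and the covariates used to balance the allocation. Study arm is not listed. The synopsis describes the same model but takes the senior HP as the cluster, not the clinic or unit.

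Section 11.2 plans for clustering. It assumes "an intraclass correlation coefficient (ICC) of 0.02 as in (18), 40% overall censoring probability and equally sized clusters of 50 patients" and arrives at 21 clusters and 1,050 patients per arm. Section 6.3.1 adds that senior HPs who share a clinic, ward or unit are allocated together, so an allocated unit can contain more than one senior HP.

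**The concern.** The standard log-rank variance assumes that patients are independent. Here whole groups of patients are allocated together, and section 11.2 itself expects outcomes within a group to be correlated. If the variance ignores this, the test statistic is too widely spread under the null hypothesis and the test rejects too often.

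The trial's main p-value is at stake. The sample size roughly doubles to pay for clustering, yet the test named for the main comparison does not take clustering into account. The one analysis that does is not assigned the comparison of arms.

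**Working it through.** **Inputs.** Two-sided alpha 0.05 and power 80% (synopsis and 11.2); hazard ratio 0.80, ICC 0.02, 40% censoring and 50 patients per cluster (11.2). The ICCs other than 0.02 and the 100 patients per unit used below are assumptions.

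**1. Reproduce the planned sample size.**
- Events (Schoenfeld): 4 × (1.960 + 0.842)² / (ln 0.80)² = 630.5, rounded up to 631. The Freedman formula gives 636.
- Patients without clustering: 631 / 0.60 = 1,052.
- Design effect: 1 + (50 − 1) × 0.02 = 1.98.
- Patients with clustering: 1,051.7 × 1.98 = 2,082, or 20.8 clusters of 50 per arm, rounded up to 21. Freedman gives 2,099 patients and the same 21.

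This matches the stated 21 clusters per arm and 2,100 patients, so the design effect of 1.98 is in the sample size.

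**2. Type I error of a log-rank test that ignores clusters.** If the true variance of the statistic is the design effect (DE) times the assumed one, the rejection rate under no effect is 2 × [1 − Φ(1.96 / √DE)]. At DE = 1.98 this is 2 × [1 − Φ(1.393)] = 0.164.

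| ICC (50 per cluster) | Design effect | Type I error |
|---|---|---|
| 0.005 (assumed) | 1.245 | 7.9% |
| 0.01 (assumed) | 1.49 | 10.8% |
| 0.02 (protocol) | 1.98 | 16.4% |
| 0.03 (assumed) | 2.47 | 21.2% |
| 0.05 (assumed) | 3.45 | 29.1% |

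**3. Check by simulation.** An ordinary log-rank test was applied to 42 clusters of 50 with no treatment effect (4,000 trials per setting, gamma frailty between clusters, about 36–37% censored). It rejected in 5.1% of trials without clustering, 12.4% at an event-indicator ICC of 0.009, and 21.5% at 0.023. A separate simulation with log-normal frailty and about 39% censoring gave 16.5%, with a variance of the log-rank z of 1.98. So the formula gives the right order of size for the log-rank test.

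**4. Effect of balanced allocation.** Section 7.3 picks among the best-balanced allocation schemes. If balance removed a share of the between-cluster variance (an assumption), the excess 0.98 in the design effect would shrink by that share:
- 25% removed: DE 1.735, type I error 13.7%
- 50% removed: DE 1.49, type I error 10.8%
- 75% removed: DE 1.245, type I error 7.9%

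**5. Power once clustering is allowed for.** Power = Φ(√(effective events / 4) × |ln 0.80| − 1.96), with 2,100 × 0.60 = 1,260 events.
- 50 patients per allocated unit: 1,260 / 1.98 = 636 effective events; Φ(2.815 − 1.960) = 80.4%.
- 100 patients per unit (assumed), same ICC: DE = 1 + 99 × 0.02 = 2.98; 1,260 / 2.98 = 423 effective events; Φ(2.294 − 1.960) = 63%.

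**The case against.** The best defense is that the protocol does contain a cluster-aware model, in the section headed Primary Analysis and directly after the log-rank sentence. A model of factors that affect readmission would naturally include the study arm, and a full list of terms is normal content for a statistical analysis plan. Section 11.3 also assigns the work to a team experienced in cluster-randomized trials. It would therefore be too strong to infer that the protocol ignores clustering in its analysis, or that the arm was meant to be left out of the model. The text establishes neither. What stands is narrower: the comparison of arms is assigned to the log-rank test, with no cluster correction named, and the Cox model is given another purpose. An analysis plan that followed this wording would inherit the problem.

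Three further points also stand.
- The 16% is conditional. It rests on a planning ICC taken from another trial's protocol, and nothing here shows that the ICC was estimated for time to readmission. A reader might take 16% as the test's actual error rate; the documents support it only at that ICC and cluster size.
- The balanced allocation in 7.3 may lower the rate, though in the illustrations above it stays over 5%.
- A reader might infer that correcting the test never costs power because 1.98 is already in the sample size. That holds only if allocated units average about 50 patients, which joint allocation of senior HPs in one ward does not guarantee.

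**Conclusion.** The point holds as a mismatch between the design and the test named for it, not as a missing detail. At the protocol's own ICC of 0.02 and 50 patients per cluster, a log-rank test without cluster correction has a two-sided type I error of about 16% against a nominal 5%: about one null trial in six. The range is about 8% at an assumed ICC of 0.005, 11% at 0.01 and 29% at 0.05. The figure assumes that the design effect carries over to the log-rank variance, which the simulations support, and that balanced allocation removes little between-cluster variance. The size of the error is uncertain. Its direction is not, for any positive ICC that balancing does not fully remove.

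The conflicting cluster unit (senior HP in the synopsis, clinic or unit in 11.3.2) is part of the same problem, because a valid correction has to work at the level at which arms are allocated.

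**What to change.** In section 11.3.2 and the synopsis:
- Name one decisive primary analysis: the study-arm term (hazard ratio, 95% confidence interval, p-value) of a Cox model that lists study arm explicitly and accounts for clustering, by a shared frailty or by a robust variance with a small-sample correction. A cluster-corrected log-rank test is an acceptable alternative. The small-sample correction matters because there are at most 42 clusters, and fewer if wards are the unit.
- Define the cluster as the unit actually allocated, meaning the clinic or ward wherever its senior HPs are allocated together, and use that definition in both places.
- Keep the Kaplan-Meier curves and the ordinary log-rank test as description only.

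The cost is wording. Section 2.9 treats a change in the form of statistical analysis as significant, so it needs ethics committee approval first. The planned 2,100 patients keep about 80% power if allocated units average about 50 patients. If wards contribute several senior HPs, section 11.2 should restate the power for the expected unit size; at an assumed 100 patients per unit and the same ICC it is about 63%.

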### 5.2 Secondary Outcomes

| Outcomes                                                                                         | Measurements                                                                                                                                                                         |
|--------------------------------------------------------------------------------------------------|--------------------------------------------------------------------------------------------------------------------------------------------------------------------------------------|
| Readmission rates at 1, 3 and 6 months after discharge                                           | Patient records tracking (patient questionnaires and/or calls, GP records, hospital records)                                                                                         |
| Number of ED visits or GP encounters within 1, 3 and 6 months after discharge                    | Patient records tracking (patient questionnaires and/or calls, GP records, hospital/ED records)                                                                                      |
| Death during follow-up of 6 months                                                               | Patient records tracking (GP records, hospital records)                                                                                                                              |
| If applicable: Reasons for readmission, ED visits, GP encounters or death                        | Patient records tracking (patient questionnaires and/or calls, GP records, hospital/ED records)                                                                                      |
| Number of drugs at discharge                                                                     | Hospital records at discharge (patient records tracking and/or calls, GP records)                                                                                                    |
| Anatomical Therapeutic Chemical (ATC) classes of the drugs prescribed/de-prescribed at discharge | Hospital records at discharge (patient records tracking and/or calls, GP records); consecutive classification at study center                                                        |

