| Proportion of potentially inappropriate medications (PIMs) at discharge                          | Hospital records at discharge (patient records tracking and/or calls, GP records); consecutive classification at study center based on 2012 Beers criteria (1) and PRISCUS list (16) |
| Number of drugs at 1, 3 and 6 months after discharge                                             | Patient records tracking and/or calls (GP records)                                                                                                                                   |
| ATC-codes of the drugs prescribed at 1, 3 and 6 months after discharge                           | Patient records tracking and/or calls (GP records); consecutive classification at study center                                                                                       |
| Proportion of potentially inappropriate medications (PIMs) at 1, 3 and 6 months after discharge  | Patient records tracking and/or calls (GP records); consecutive classification at study center based on 2012 Beers criteria (1) and PRISCUS list (16)                                |
| Patients' quality of life at discharge                                                           | EQ-5D-3L-scale                                                                                                                                                                       |

|                                                                   |                |
|-------------------------------------------------------------------|----------------|
| Patients' quality of life
at 1, 3 and 6 months after discharge | EQ-5D-3L-scale |
|-------------------------------------------------------------------|----------------|

The following covariates will be used for balanced cluster allocation and subgroup analyses:

| Covariates                                                         | Measurements                                                            |
|--------------------------------------------------------------------|-------------------------------------------------------------------------|
| Patient characteristics
(age, sex)                              | Patient declaration at inclusion                                        |
| Hospital type
(A-D  ; University or Non-University) | Questionnaire/interview with decision maker
at recruitment of clinic |

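### Patient-level secondary outcomes are assigned to t, chi-square and Wilcoxon tests with no adjustment for clustering, although the sample size rests on a design effect of 1.98

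*Protocol*

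**What the plan says.** Protocol section 11.3.2 assigns the secondary outcomes to a parametric test (the t-test) or non-parametric tests (chi-square "and Wilcoxon test) will be used where appropriate"). The Statistical Considerations entry of the synopsis gives the same rule, with U tests in place of Wilcoxon.

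The outcomes concerned are listed in section 5.2. Those measured on patients are readmission rates, ED and GP contacts ("Number of ED visits or GP encounters within 1, 3 and 6 months after discharge"), death, drug counts ("Number of drugs at 1, 3 and 6 months after discharge" as well as at discharge), potentially inappropriate medications and EQ-5D.

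Section 6.3.1 randomises senior hospital physicians (HPs) and allocates all those in one clinic, ward or unit jointly. Clustering appears in the planned analyses only in the Cox model for factors affecting readmission. That model takes clinics or units as clusters in section 11.3.2 and senior HPs in the synopsis. Beyond this, section 11.3 offers only a general assurance: "All statistical analyses will be carried out by the study team experienced in the conduct of cluster-randomized trials".

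**The concern.** In their standard form the named tests treat patients as independent. Patients discharged under the same senior HP or ward share prescribing habits and discharge routines, so their outcomes may be correlated. Ignoring that makes standard errors too small and p-values too low.

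These outcomes carry weight. The primary objective (section 4.2) and the hypothesis (section 11.1) both include health outcomes and quality of life and refer to section 5.2. Drug counts and inappropriate medications bear on the overall aim of reducing polypharmacy (section 4.1). An inflated error rate could lend chance findings to the case for dissemination.

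The plan is also inconsistent with itself, because the sample size section pays for clustering and the secondary analysis does not use it.

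**Working it through.** **Inputs.** From the synopsis: "We assumed a two-sided alpha of 0.05, a power of 80%, an intraclass correlation coefficient (ICC) of 0.02". From section 11.2: the effect "corresponds to a hazard ratio of 0.80 between intervention and control group participants"; "40% overall censoring probability and equally sized clusters of 50 patients"; and the result, "42 senior HPs and 2'100 patients in total will need to be included".

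**Step 1: reproduce the sample size.**
- Events by Schoenfeld: 4 × (1.960 + 0.842)² / (ln 0.80)² = 631. By Freedman: ((1 + 0.80)/(1 − 0.80))² × (1.960 + 0.842)² = 636.
- Patients with 60% having an event: 631/0.60 = 1,052; 636/0.60 = 1,060.
- Design effect: 1 + (50 − 1) × 0.02 = 1.98.
- Inflated total: 1,052 × 1.98 ≈ 2,082; 1,060 × 1.98 ≈ 2,099. Dividing by 100 (two arms, 50 per cluster) gives 20.8 and 21.0, hence 21 clusters per arm and 2,100 patients.

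The stated figure is reproduced. Without the inflation the total would be about 1,050 to 1,060. With a design effect based on events only, 1 + (30 − 1) × 0.02 = 1.58, it would be 17 clusters per arm. So the plan's figure implies a design effect of 1.98.

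**Step 2: the named tests under that design effect.** An unadjusted test uses a standard error too small by √1.98 = 1.41. Its true two-sided error is 2 × (1 − Φ(1.96/1.41)) = 16.4%. A 95% interval using the same standard error covers 100 − 16.4 = 83.6%. The effective sample size is 2,100/1.98 ≈ 1,061.

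**Step 3: check by simulation.** With 21 clusters of 50 per arm, ICC 0.02 and no treatment effect, the rejection rates were 17.2% (t-test), 15.4% (Wilcoxon) and 16.6% (chi-square, event rate 20.1%). A t-test on cluster means rejected in 5.0%.

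**Step 4: range of ICC.** The protocol gives only 0.02, and gives it for the primary outcome. The other rows are assumptions, all at 50 per cluster.

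| ICC | Design effect | SE ratio | Type I error | Effective N |
|---|---|---|---|---|
| 0.005 | 1.245 | 1.12 | 7.9% | 1,687 |
| 0.01 | 1.49 | 1.22 | 10.8% | 1,409 |
| 0.02 | 1.98 | 1.41 | 16.4% | 1,061 |
| 0.05 | 3.45 | 1.86 | 29.1% | 609 |
| 0.10 | 5.90 | 2.43 | 42.0% | 356 |

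**Step 5: the cluster unit.** Because HPs of one ward are allocated together, the unit actually randomised can hold more than 50 patients. As an illustration only, two HPs per ward at ICC 0.02 give a design effect of 1 + 99 × 0.02 = 2.98 and an error of about 26%.

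**The case against.** The best defence is that the analysis plan is not at hand and may specify clustered methods, that the tests are qualified as applying where appropriate, and that the team has experience of cluster trials. This does not remove the point. The protocol names specific tests in two places. The qualifier most naturally governs the choice between parametric and non-parametric tests, and experience is not a method. Section 2.9 also treats a change in the form of statistical analysis as a substantial amendment, so a later plan should not quietly replace these tests.

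Several stronger readings are tempting, and the documents do not support them:
- **All secondary outcomes are affected.** The synopsis also lists HP feasibility ratings, use of the communication offer, and barriers and enablers. HP ratings and records are not data on patients nested under an HP, so the design effect does not apply to them.
- **Patients who die or drop out have their visit counts treated as fully observed.** The text does not say so. Section 11.4 plans multiple imputation with a complete-case sensitivity analysis, and section 9.2 describes retrieving missing data. Handling of death and time at risk in the counts is left open, which is detail an analysis plan can supply.
- **Repeated measures make the tests invalid.** A comparison at a single time point is not invalid for that reason. A longitudinal model would be a gain in efficiency.
- **The planned secondary confidence intervals are wrong.** The analysis section mentions 95% intervals only for baseline characteristics. The 84% coverage applies to any interval that might be derived from these tests.
- **Clustering in prescribing outcomes probably exceeds 0.02.** Nothing in the protocol shows this. Section 11.2 takes 0.02 from a cluster trial on polypharmacy, and the true values could lie on either side.
- **Readmission has no clustered analysis.** The Cox model covers factors affecting readmission; what lacks one is the comparison of proportions at 1, 3 and 6 months.

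**Conclusion.** The point holds for the patient-level outcomes of section 5.2. The protocol states a rule for them that ignores clustering, while its own sample size implies that clustering nearly doubles the variance. At ICC 0.02 and equal clusters of 50, a nominal 5% test has a true type I error of about 16%. That rests on carrying the primary outcome's ICC over to the secondary outcomes. Over the assumed range of 0.005 to 0.10 the error is about 8% to 42%, so it exceeds 5% throughout and only its size is uncertain. The sample size and the comparison of the primary outcome do not depend on these tests.

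**What to change.** Replace the sentence on secondary outcomes in section 11.3.2 and its counterpart in the synopsis. For every patient-level outcome in section 5.2, name a cluster-adjusted method: mixed models, GEE with a small-sample correction (there are at most 42 clusters, fewer if counted by ward), or t-tests on cluster-level summaries. Adjust for the covariates used in allocation. The last option keeps a test the protocol already names and held its level in the simulation.

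State one cluster unit that respects joint allocation by clinic or ward (section 6.3.1), and reconcile the synopsis, which uses senior HPs, with section 11.3.2, which uses clinics or units.

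Optional, as an efficiency gain and not the correction of an error: a longitudinal model over visits for drug counts and EQ-5D, and a log time-at-risk offset for visit counts.

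The cost is amended wording and slightly more analysis work, with no new data. Intervals will be wider than unadjusted ones, which is the correct reflection of the design.
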